## Abstract

**Background:**

The effect of telemedicine solutions in diabetes remains inconclusive. However, telemedicine studies have shown a positive trend in regards to glycemic control. The telemedicine interventions that facilitate adjustment of medication seems to improve glycemic control more effectively. Hence, it is recommended that future telemedicine studies for patients with diabetes include patient-specific suggestions for changes in medicine. Hence, the aim of the trial is to explore the effect of telemonitoring in patients with type 2 diabetes (T2D) on insulin therapy.

**Methods:**

The trial is an open-label randomized controlled trial with a trial period of 3 months conducted in two sites in Denmark. Patients with T2D on insulin therapy will be randomized (1:1) to a telemonitoring group (intervention) or a usual care group (control). The telemonitoring group will use a continuous glucose monitor (CGM), an insulin pen, an activity tracker, and smartphone applications throughout the trial. Hospital staff will monitor the telemonitoring group and contact the subjects by telephone repeatedly throughout the trial period. The usual care group will use a blinded CGM the first and last 20 days of the trial and will use a blinded insulin pen for the entire period.

The primary endpoint will be changed from baseline in CGM time in range (3.9–10.0 mmol/L) 3 months after randomization. Secondary endpoints include change from baseline in glycated hemoglobin (HbA1c), total daily dose, time above range, and time below range 3 months after randomization. Exploratory endpoints include health-related quality of life, diabetes-related quality of life, etc.

**Discussion:**

The DiaMonT trial will test a telemonitoring setup including various devices. Such a setup may be criticized, because it is impossible to determine which element(s) add to the potential effect. However, it is not possible and counterproductive to test the elements individually, since it is the full telemedicine setup that is being evaluated. The DiaMonT trial is the first Danish trial to explore the effect of telemonitoring on patients on insulin therapy. Thus, the DiaMonT trial has the potential to form the basis for the implementation of telemedicine for patients with T2D in Denmark.

**Trial registration:**

ClinicalTrials.gov NCT04981808. Registered on 8 June 2021.

## Introduction

### Background and rationale

Diabetes is a major problem for the global health. In 2017, it was estimated that 8.4% of the adult global population had diabetes. This number is expected to increase to approximately 9.9% (425 million) in 2045 due to an increase in unhealthy diets, obesity, physical inactivity, etc [1–4]. Approximately 90-95% of patients with diabetes have type 2 diabetes (T2D) [5, 6].

Maintaining optimal glycemic control is crucial for both the prevention and control of diabetes-related complications [7]. However, optimal glycemic control is difficult to maintain. This is primarily due to the fact that it is challenging to estimate the correct dose of diabetes medication in order to avoid hypo- and hyperglycemia [7, 8]. Large US studies indicate that less than 50% of patients with diabetes reach their treatment goals [9, 10]. This suggests that the results obtained in research are not reflected when observing patients in the real world [11]. An important reason for this is that patients do not adhere to the prescribed medical treatment [11]. Therefore, medical treatment may be supplemented by telemedicine with an eye to achieving the desired treatment goals.

In telemedicine, technology is used to support patients with diabetes in disease management over a distance [12, 13]. The telemedicine solutions are very diverse and can range from simple reminders via Short Message Service (SMS) to more complex solutions where the patient does various measurements at home, which are monitored over the distance by a health care professional [14–20]. As diabetes care is primarily handled outside a hospital setting in Denmark and other countries, the potential of telemedicine in supporting patients with diabetes in achieving their treatment goals is promising. In addition, telemedicine may be relevant for those patients who are limited in their opportunities for physical attendance for a variety of reasons [21].

In a 2017 systematic review, it was concluded that telemedicine solutions are a safe way to provide support for self-care for patients with diabetes [22]. Moreover, the use of telemonitoring is cost-effective in diabetes management [23]. In contrast, previous reviews on the effect of telemedicine solutions have shown divergent results, though with a positive trend in regards to glycemic control [13, 24–27]. A recent comprehensive review and meta-analysis by Faruque et al. [13] showed an improvement in glycated hemoglobin (HbA1c) in patients who offered telemedicine as a supplement to regular therapy. The results indicated that future telemedicine studies for patients with diabetes should include tailored patient-specific suggestions for changes in medicine, as the telemedicine interventions facilitating adjustment of medication improved glycemic control more effectively [13]. Thus, there is a need to develop a telemedicine solution with the possibility to customize the treatment depending on the individual patient and medical needs.

The Adherence through Cloud-based Personalized Treatment for Type 2 Diabetes project (ADAPT-T2D) has an overall objective of improving treatment goals for patients with type 2 diabetes. This has endeavored through the development and testing of a telemedicine solution for patients with type 2 diabetes who are on insulin therapy. The first trial in the ADAPT-T2D project is the *Dia*betes tele*mon*itoring of patients in insulin *t*herapy (DiaMonT) trial. It is particularly difficult for patients on insulin therapy to adhere to treatment goals, as a number of barriers are associated with insulin therapy [28]. Such barriers may be related to the patient, medication factors, or system factors. For instance, patients may forget or fear to take medication, the medication regimen may be very complex, expensive, or have side effects, and the patient support may be inadequate [28, 29]. Therefore, this particular group of patients is the population of interest in the present trial.

### Objectives

The aim of the trial is to explore the effect of telemonitoring in patients with T2D on insulin therapy.

### Trial design

The design is an open-label randomized controlled trial with a trial period of 3 months. Patients with T2D in telemonitoring (intervention) are compared with patients with T2D in usual care (control). Neither the included patients nor the clinical staff involved in the trial can be blinded to assignment as they will know whether a patient is being telemonitored or not. The data analysis will be performed by researchers from the project group, who will not be blinded to group assignments for practical and financial reasons.

The trial will be carried out in accordance with the Helsinki Declaration and the principles of good clinical practice (GCP). The trial has been approved by the Regional Ethical Committee of North Jutland (N-20200068).

## Methods: Participants, interventions, and outcomes

### Study setting

The trial will be conducted in two sites in Denmark: Steno Diabetes Center North Denmark (Aalborg University Hospital) and Steno Diabetes Center Zealand (Nykøbing Falster Hospital).

### Eligibility criteria

We aim to include 400 participants. The participants will all be patients with T2D who are already treated with insulin. The participants will receive an insulin pen from Novo Nordisk A/S, which only works with Novo Nordisk products. Therefore, participants who are not treated with Novo Nordisk insulin will be shifted to Novo Nordisk basal insulin (Tresiba®) by trial initiation. If the participants should have any problems, concerns, or questions related to the shift in insulin, a telephone hotline with trained staff will be available for the participants 24/7.

Participants will be included based on the following criteria: Women and men ≥ 18 years, T2D diagnosis for ≥ 12 months, residence in Region North Denmark or Region Zealand, in treatment with insulin, being able to use a smartphone along with the other devices to be used in the trial, and able to understand and read Danish. Diagnosis of T2D was defined as either (1) glycated hemoglobin A1c ≥ 48 mmol/mol; (2) venous plasma glucose ≥11.1 mmol/l incl symptoms of polyurea, polydipsia, unexplained weight loss, or recurrent infections; or (3) venous plasma glucose ≥ 7.0 mmol/l or a 2-h plasma glucose ≥ 11.1 mmol/l after an oral glucose tolerance test. Participants will be excluded based on the following criteria: pregnancy or breastfeeding, major surgery planned during the trial period, participation in other trials, and terms that, in the opinion of the investigator or subinvestigators, render the participant unfit to conduct the trial, including lack of understanding of the trial or lack of physical or cognitive ability to participate.

### Recruitment

The participants will be recruited by use of multiple approaches. First of all, the participants will be recruited at Aalborg University Hospital and at Nykøbing Falster Hospital when attending endocrinology clinic visits. For recruitment purposes, posters will be displayed at the endocrinology clinic at both hospitals with information about the trial. Hospital staff will hand out a recruitment leaflet to interested patients. When visiting the endocrinology clinic, patients can consent to being contacted by representatives from the ADAPT-T2D project team in order to receive more detailed information about the trial. Additionally, a patient group has consented that they may be contacted in connection with initiation of new trials at the endocrinology clinic at Aalborg University Hospital. This group of patients will be contacted by phone and will later receive further information about the trial by mail if interested. Moreover, the recruitment will take place through advertising in newspapers, in the Danish diabetes magazine, on social media, in relevant patient organizations, and on the websites of the involved Danish regions.

### Informed consent

Interested patients will be called in for an information interview with the possibility of a companion. This is described in the participant information letter, which is sent or handed over to the patient prior to the interview. The participant information letter also explains the purpose and design of the trial. The information interview takes place at Aalborg University Hospital in a private room. The information interview is conducted by the investigator, a subinvestigator, or a delegated project team member with the necessary professional knowledge. During the interview, the participant will be made aware of the possibility of reflection time prior to giving informed consent. Consent can be withdrawn at any time and without justification. Only when the informed consent has been obtained with the signature of both the participant and the investigator or a subinvestigator, the trial can begin.

### The randomization process

At the beginning of the trial, the participant will be randomized to either the telemonitoring group or the usual care group during a visit to the endocrinology clinics at Aalborg University Hospital or Nykøbing Falster Hospital. Randomization will be performed in RedCap (2020 Vanderbilt University) based on a computer-generated random list (ratio 1:1). The list will be concealed in RedCap until interventions are assigned. Prior to randomization, the participants will be informed about the trial and sign informed consent. Medical laboratory technicians, nurses, and researchers will enroll the participants, give them information regarding the trial, obtain informed consent, and assign the participants to interventions. The trial is open-labeled, since both participants and staff involved in the trial will know whether the participants are being telemonitored or not.

Basic baseline information about the participants will be obtained at trial start in addition to questionnaire data (Table 1). Moreover, a venous blood sample will be drawn to cover secondary endpoints as well as baseline information. A lab technician/nurse will be responsible for the blood sampling.

**Table 1 Tab1:**
[figure not shown]
The deployment of questionnaires in the two study groups

*Abbreviations: SF-12* short form 12 (measuring health-related quality of life) [30], *DIDP* DAWN2 Impact of Diabetes Profile (measuring the perceived impact of diabetes) [31], *TUQ* telemedicine usability questionnaire (measuring the quality of the telemedicine intervention) [32], *SHE* Subjective Experience Health questionnaire [33]

### The intervention

#### The telemonitoring group

The telemonitoring group will be provided with a continuous glucose monitor (CGM), a new smart pen from Novo Nordisk A/S, an activity tracker, and a smartphone (unless the participant prefers to use his/her own smartphone). The smart pen will be used for long-acting insulin for all participants. A second smart pen will be provided to those participants who are also on short-acting insulin. The participants will be trained to use the technologies provided at trial inclusion.

The telemonitoring group will use the distributed devices continuously to collect, log, and transfer tissue glucose levels, insulin administration, activity, and sleep at home for the entire trial duration. Laboratory technicians/nurses affiliated with the endocrinology clinics will perform the monitoring. The frequency of monitoring is tailored to the needs of each individual participant. The monitoring laboratory technicians/nurses will contact the participant by phone at least three times — at 1 week, 1 month, and 2 months after inclusion in the trial. Participants may be contacted on an ongoing basis if it is considered relevant by the monitoring lab technicians/nurses. The first phone call, after 1 week, is performed with an eye to ensuring that the participants have started the monitoring successfully and understand how to use the devices. During the calls after one month and 2 months after inclusion, the monitoring lab technicians/nurses will talk to the participants about their data from the past month. The ongoing calls are expected to have a more specific focus. Such calls will be performed if the lab technicians/nurses monitor data that they consider to be unusual. The frequency of such calls will thus rely on the individual assessment of the lab technicians/nurses, as they are not supported by any decision support algorithms. The monitoring lab technicians/nurses may give treatment advice during all calls and potentially change insulin doses based on the monitored data (after consulting a doctor). The participants are welcomed to call the lab technicians/nurses all weekdays during the intervention period if they have any questions regarding their data. All calls to participants are recorded in the participants’ respective journals.

For technical challenges, participants can contact research staff at Steno Diabetes Center by phone via a technical support line.

#### The usual care group

The usual care group will receive standard of care in accordance with Danish guidelines. In addition, a new Novo Nordisk insulin smart pen is provided to all participants in the usual care group. The smart pen will be used for long-acting insulin for all participants. A second smart pen will be provided to those participants who are also on short-acting insulin. The pens received by the usual care group will be blinded to ensure that participants are unable to see their data. The pens will collect data used for later analysis and comparison of adherence to insulin prescription in the intervention group and the control group. In addition, the usual care group will be provided with a continuous glucose monitor (CGM), which they will be asked to wear the first and last 20±2 days of the trial period. The CGM will also be blinded so that the participants are unable to see their data. The CGM data will be used for analysis of the primary and secondary outcomes. Thus, participants in the usual care group will receive usual care with an addition of the blinded devices. No changes in treatment, including medicine/dosage, will be performed based on the blinded devices, as neither patients nor clinical staff will have access to the data. The control group will not be compensated financially for their participation in the trial. However, by the end of trial, the monitoring lab technicians/nurses will offer to print out the data from the blinded devices and go through them with the participants in the usual care group.

The authors hypothesize that the telemonitoring intervention will significantly improve time-in-range compared to usual care.

#### Criteria for discontinuing

The trial will be terminated in the event of any serious adverse events related to the trial as considered by the primary investigator. The trial is stopped for each participant if severe hypoglycemia, ketoacidosis, or severe hyperglycemia is recorded and related to the trial based on the primary investigator’s assessment.

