#### End of trial

At end of trial, participants from both groups visit the endocrinology clinic again. The participants are encouraged to answer various questionnaires and a laboratory technician/nurse will take a venous blood sample. The flow of the trial design is illustrated in Fig. 1.

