#### Exploratory endpoints

The exploratory endpoints are based on questionnaires and monitoring data, and include the following:5)Change from baseline in CGM endpoints 3 months after randomization: number of days worn, percentage of time active, mean glucose, glycemic variability, time in hyperglycemia (>13.9 mmol/L), time in hypoglycemia (<3.0 mmol/L), episodes (hypoglycemia and hyperglycemia) 15 min and area under the curve.6)Use of the telemonitoring equipment: The frequency of use of the telemonitoring equipment during the trial is assessed directly from the delivered devices.7)Telemonitoring usability: Data is collected via the Telemedicine Usability Questionnaire. The telemedicine group will answer the questionnaire at the 3-month assessment.8)Diabetes-related quality of life: Between group differences measured by the DIDP questionnaire at baseline and at the 3-month assessment.9)Quality of Life: Between group differences measured by the SF-12 questionnaire at baseline and at the 3-month assessment.10)Adherence to insulin dosing and timing. Any differences in the use of insulin between the two groups are examined based on data from the insulin pens.11)Number of hypoglycemic events 3 months after randomization.

In addition, qualitative interviews will be conducted with selected participants in order to gain deeper insight into the participants’ experience of telemonitoring.

Hospital staff will make appointments with the participants for the final visit, during which the final data will be collected. Should a participant not show up for the appointment, hospital staff will contact the participant by telephone to schedule a new appointment. Participation in the final visit is considered to be completion of trial regardless of the degree of use of technologies. The trial ends after the last participant’s final visit.

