### Statistical analysis

Sample size calculation is based on the following formula:$$n=\frac{2{\sigma_d}^2}{\tau^2}{\left({z}_{a/2}+{z}_{\beta}\right)}^2$$

*τ* is the minimum detectable difference in mean and *σ*_*d*_ is the standard deviation of the difference. Based on an assumed difference in reduction of CGM time in the range of 80 min (*τ* =  − 80), a standard deviation of the difference of 220 min (*σ*_*d*_ = 220) [34], a significance level of 0.05 and a power of 0.9, the number of participants is 320. With an estimated dropout rate of 25%, 400 participants must be included. The large dropout rate is primarily expected in the usual care group. To minimize loss to follow-up, the trial staff will provide the participant in the usual care group with a printout of their data at study completion and offer a consultation regarding the data.

A variety of statistical methods will be applied to investigate the objectives of the trial after end of trial. No analysis is planned during the data collection period. All statistical methods will be applied on the Full Analysis Set that includes all randomized participants. Imputation of missing data is described below.

Change in CGM metrics and total daily insulin dose will be calculated as the difference between mean of the metric, e.g. time in range, or total daily insulin dose the 2 weeks before end of trial and the 2 weeks after randomization. Using data from all patients, the primary endpoint will be investigated with the following primary analysis. The primary analysis is performed with a statistical model that includes multiple imputation, where patients without CGM at scheduled visits get their CGM time in range imputed. An analysis of variance model with the region as a factor and CGM time in range at baseline as a covariate is used to estimate the effect of telemonitoring on CGM time in range. Sensitivity analysis with similar configurations will be applied to subgroups.

The secondary endpoints will be investigated using statistics, models, and algorithms that include differential equations in compartment modeling, as well as algorithms in Machine Learning.

All participants included in the trial will be included in the statistical analyzes. The statistical significance level of 5% is used in the trial (*p* < 0.05). Participation in the final visit is considered to be completion of trial regardless of the degree of use of technologies. The trial ends after the last participant's final visit.

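### The individual stopping rule ends the trial, not only the intervention, for a participant, so observable 3-month outcomes may be lost (minor wording fix)

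*Protocol article*

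**What the plan says.** The section Criteria for discontinuing holds two rules. The first concerns the whole study: "The trial will be terminated in the event of any serious adverse events related to the trial". The second concerns the individual: "The trial is stopped for each participant if severe hypoglycemia, ketoacidosis, or severe hyperglycemia is recorded and related to the trial". The primary investigator judges relatedness in both.

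The endpoints are 3-month values. Under Statistical analysis, change in the CGM metrics and in daily insulin dose compares "the 2 weeks before end of trial and the 2 weeks after randomization". HbA1c comes from the blood sample at the final visit. The exploratory endpoints include "Number of hypoglycemic events 3 months after randomization".

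Three further statements bear on what happens to a stopped participant:

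- End of trial: "At end of trial, participants from both groups visit the endocrinology clinic again".
- Exploratory endpoints, repeated under Statistical analysis: "Participation in the final visit is considered to be completion of trial regardless of the degree of use of technologies".
- Statistical analysis: "All statistical methods will be applied on the Full Analysis Set that includes all randomized participants", and "patients without CGM at scheduled visits get their CGM time in range imputed".

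CGM is worn throughout in the telemonitoring group, but only for the first and last 20±2 days in usual care.

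**The concern.** Stopping a treatment and stopping follow-up are different acts. The individual rule does not separate them, and it uses the same term, the trial, that the sentence before it uses for the whole study. Staff who follow it to the letter would collect nothing further from that participant.

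The trigger is an extreme glucose event, so the missing values would not be a random subset. Multiple imputation keeps the participant in the all-randomized analysis. It would, however, fill in time in range largely from participants who had no such event, in place of a value that could have been observed. CGM time below range after the stop would not be seen at all. The people affected are few, but they tell most about hypoglycaemia.

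**Working it through.** **Reading the text.** The question is whether any statement secures the 3-month data after an individual stop.

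- The section sits under the heading The intervention, which suggests that only the intervention is meant. But the rule covers each participant, and usual care has no telemonitoring to stop.
- End of trial makes no exception for stopped participants, but does not mention them.
- The completion definition covers people who use the devices little. It does not address someone whose trial has been stopped.
- The rebooking procedure in the section Exploratory endpoints covers missed appointments only.

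None of these bars a stopped participant from the final visit, and none secures it.

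**Reproducing the plan's figure.** Inputs from Statistical analysis: difference 80 min, SD 220 min, two-sided 5% level, power 0.9.

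- n per arm = 2 × 220² / 80² × (1.96 + 1.2816)² = 15.125 × 10.51 ≈ 159, or 318 in total. The plan states 320, so the figure is reproduced.
- Design standard error with 160 per arm: 220 × √(2/160) = 24.6 min.
- Power at 80 min: Φ(80/24.6 − 1.96) = 90.2%.

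**Illustrative shift in the treatment difference.** The stop rate, the gap between unseen and imputed time in range, a 90-day trial period and uniform stop timing are all assumptions. Randomizing 400 participants 1:1 gives 200 per arm.

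- Stopped in one arm only: 1% to 2% of 200 = 2 to 4 people.
- Gap: 100 to 200 min/day.
- Shift = share × gap: 0.01 × 100 = 1 min to 0.02 × 200 = 4 min/day.
- Relative to the standard error: 1/24.6 = 4% to 4/24.6 = 16%.
- Power if the 80 min effect is shifted by 4 min: Φ(76/24.6 − 1.96) = 87.1%, or Φ(84/24.6 − 1.96) = 92.7%.

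**Allowing for timing.** A stop before day 90 − 14 = 76 loses the whole final window: 76/90 = 84.4%. The other 14/90 = 15.6% lose about half of it on average. The effective fraction is 0.844 + 0.5 × 0.156 = 0.922, so the shift is 0.9 to 3.7 min/day.

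**Pure loss of information.** As a worst case in which imputation recovers nothing, 25% dropout leaves 300 evaluable and power of 88.3%. Assumed further losses give:

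| Stopped, share of 400 | People | Evaluable | Power |
|---|---|---|---|
| 0.5% | 2 | 298 | 88.1% |
| 1% | 4 | 296 | 87.9% |
| 2% | 8 | 292 | 87.4% |
| 5% | 20 | 280 | 86.0% |

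**What CGM would remain in usual care.** With uniform timing, (70 − 20)/90 = 56% of stops fall between the two wear periods. The ±2 days give (68 − 22)/90 = 51% to (72 − 18)/90 = 60%. These participants would have only the first period.

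**The case against.** The strongest reply is that the article condenses a fuller protocol, and that procedures after an individual stop may be set out there. That would answer a complaint about missing detail. It does not fully answer this one, because the article states a rule and the rule's wording ends the trial for the participant. An analysis plan cannot recover data that the sites did not collect.

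The second reply is that the surrounding text leans towards a milder reading. This stands in part. A reader might infer that the protocol excludes stopped participants from the final visit or from the analysis. The documents do not support that: no sentence bars the visit, and the Full Analysis Set includes everyone randomized.

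The third reply is that the trigger is narrow, and this stands. The event must be severe, recorded and judged trial-related, and any related serious adverse event already ends the whole trial under the first rule. The individual rule matters only for what remains. In usual care no treatment change follows from the blinded devices, so that group of stops may be nearly empty and the 51% to 60% range may describe very few people.

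Some information also survives. Related adverse events are recorded and reported, consent gives access to the patient journal, so later hypoglycaemic events that were medically recorded may be retrievable, and telemonitoring CGM exists up to the stop. Later CGM time below range does not.

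A reader might also infer that stopping will be uneven between the arms and will bias the result one way, because staff see CGM data only under telemonitoring. That is possible, but the documents give no rate for either arm. Similar stopping and gaps in both arms would largely cancel.

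**Conclusion.** The point holds as a minor one. Taken at its word, the individual rule creates avoidable missing 3-month data after an event related to the endpoints, and the text that softens it does not secure those data. It covers only events that do not terminate the whole trial.

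The effect on the primary result is probably small and its direction is unknown. The figure of at most 1 to 4 min/day rests wholly on assumed stop rates and gaps. Its upper end needs 2% stopped in one arm only and an error of 200 min per person, which is 2.5 times the design effect (200/80). In the information-loss illustration, stopping 0.5% to 2% costs less than 1 percentage point of power. The case for change is that the data can be kept at little cost, not that the trial's conclusion is at risk.

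**What to change.** Reword the individual rule so that the telemonitoring intervention is stopped as the investigator judges while follow-up continues. With the participant's consent, the 3-month visit, the HbA1c sample and the final-period CGM are still obtained. Whether that CGM is blinded should be decided on clinical safety grounds and not required. Hiding readings after a severe glycaemic event could do harm, above all for someone in the telemonitoring group who could see them before.

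Use the observed values in the Full Analysis Set, keep imputation for values that really are missing, and report individual stops by arm.

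The cost is a change of wording. The visit, the blood sample and the final CGM period are already planned in both arms, and the sample size does not change. Some stopped participants may decline, and CGM wear after a severe event needs case-by-case clinical judgement.
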